### Objectives {7}

In the present study, the main aim is to investigate whether the serious game is more effective in improving sibling quality of life and adjustment to the disability of the brother or sister, compared to waitlist control group. Secondly, it will be investigated whether the serious game is more effective compared to the waitlist control group in improving different aspects of psychosocial well-being. These include the following: (1) siblings’ self-esteem, (2) siblings’ perceived social support, (3) sibling relationship with the brother or sister with a disability, (4), siblings’ coping skills, and (5) parent-child relationship. Thirdly, the social validity of the serious game will be investigated in order to evaluate the desirability, applicability, and subjective evaluation of the game. Finally, exploratory analyses will be executed to investigate possible moderators and the effect of the intervention on parenting self-efficacy.

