### Trial design {8}

The effectiveness of the serious game will be examined using a parallel superiority randomized controlled trial (RCT) design with quantitative and qualitative assessments on three measuring moments: pre-test (T0), post-test (T1; 5 weeks after pre-test), and follow-up (T2; 6–8 weeks after post-test). The children will be randomly assigned to two groups of equal size using stratified block randomization: an experimental group that will play the serious game and a waitlist control group.

The methods of this study are reported according to SPIRIT 2013 Explanation and Elaboration: Guidance for protocols of clinical trials [35].

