### Sample size {14}

Using GLIMMPSE 3.0 [63], the required sample size to conduct multivariate linear mixed models for the primary outcomes quality of life and sibling adjustment to the disability of the brother or sister is calculated. The sample size is estimated with an alpha of 0.05 and a target power of 0.80 and is based on an interaction effect hypothesis, including between (intervention) and within (measurement point) variance. Correlations between measurement points are estimated to be 0.60 (T0–T1; T1–T2) and 0.40 (T0–T2), based on previously found test-retest correlations on the PedsQL [64]. The correlation between the outcomes is estimated to be 0.30. This estimate is based on a previously found correlation between the SPQ and a measure of wellbeing and adjustment (Strengths and Difficulties Questionnaire; SDQ), as no information about the correlation between de SPQ and a measure of quality of life was available [65]. A scale factor of 1.2 for variability is inserted in the sample size calculation, in order to be more conservative.

For both quality of life and sibling adjustment to the disability of the brother or sister the child-report means and standard deviations from previous sibling studies are used [41, 66]. For the control group, no change is expected on the outcome measures. For the intervention group, change is expected gradually. The expected total change (at T2) on quality of life is based on the Minimal Clinically Important Difference [67]. The expected total change on sibling adjustment to the disability of the brother or sister is based on the measured change in a previous sibling intervention study [41]. No change in standard deviations is expected on all measurement points.

The computed sample size calculation based on the beforementioned parameters results in a required sample size of 134, with 67 participants in the intervention group and 67 participants in the waitlist control group. Based on two previous intervention studies [22, 29], a dropout rate of 15% is accounted for. The total required sample size is therefore 154. This includes 154 siblings and their 154 parents.

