## Statistical methods

### Statistical methods for primary and secondary outcomes {20a}

In the current study, quantitative data will be analyzed using IBM SPSS Statistics 27 [69], and qualitative data will be analyzed using ATLAS.ti. 22 [70].

The primary and secondary objectives, as well as the exploratory analysis on parenting self-efficacy, will be answered by computing the linear mixed-effects model procedure (MIXED). To test the effect of the intervention, the main effects of intervention and time, together with the interaction effect between intervention and time, will be included in the model. The primary objectives will be analyzed multivariate, whereas the secondary objectives are analyzed univariate. For the latter, the Bonferroni correction will be used to determine the alpha level. Child-report and parent-report outcomes will be analyzed separately. Cohen’s Ds will be calculated to determine the effect size. The answers to the open-ended questions will be analyzed using thematic coding with conventional qualitative content analysis [71]. The outcomes of the PAIR will be analyzed in both a quantitative way using the manual [48]. Thematic analysis of the drawings will also be executed according to the procedure described in Guidotti et al. [49]. The drawings of the PAIR are scored by two independent researchers. Intra-class correlations will be calculated to assess the inter-rater reliability.

For social validity, the mean scores will be reported. Additionally, one sample *t*-tests will be executed in order to test if the mean score significantly differs from the neutral score (3). Conventional qualitative content analysis will be used to analyze the answers to the open-ended evaluation questions [71].

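### The primary intervention-by-time test names no visit or contrast and leaves T0 unadjusted, although the sample size places the clinically important change at T2

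*Protocol article*

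**What the plan says.** The objectives section {7} states that "the main aim is to investigate whether the serious game is more effective in improving sibling quality of life and adjustment to the disability", with no time point. The trial design section {8} sets three visits: "pre-test (T0), post-test (T1; 5 weeks after pre-test), and follow-up (T2; 6–8 weeks after post-test". Table 2 shows both primary outcomes collected at all three.

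The statistical methods section {20a} describes the effect test as a mixed model in which "the main effects of intervention and time, together with the interaction effect between intervention and time, will be included in the model". The two primary outcomes are analysed multivariately. No visit, contrast or direction is singled out. Cohen's d is promised without saying for which visit.

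The sample size section {14} is more specific about the effect. The calculation "is based on an interaction effect hypothesis, including between (intervention) and within (measurement point) variance". Controls are assumed not to change, while "For the intervention group, change is expected gradually". Then: "The expected total change (at T2) on quality of life is based on the Minimal Clinically Important Difference". The other inputs are "The sample size is estimated with an alpha of 0.05 and a target power of 0.80" and "Correlations between measurement points are estimated to be 0.60 (T0–T1; T1–T2) and 0.40 (T0–T2"). The correlation between the outcomes is 0.30, and the result is 134 children, 67 per arm.

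**The concern.** The plan says where the meaningful effect should appear, at T2, but its effect test is not directed there. With time as a factor, the interaction asks only whether the two arms' profiles differ in some way over three visits. A significant result could come from T1, from T2, or from opposite movements, so it does not by itself establish the T2 benefit on which the sample size rests. With no visit ranked first, the choice of which one to headline stays open until results are known. Blinding the analysts does not fully close this, because emphasis can be chosen at reporting.

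There is also a cost in efficiency. A model with free intervention, time and interaction terms treats T0 as a third outcome with its own arm difference. Randomisation makes the expected T0 difference zero, and the model does not use that.

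**Working it through.** **Inputs from {14}.** Correlations over time 0.60 (T0–T1, T1–T2) and 0.40 (T0–T2); outcome correlation 0.30; 67 per arm; alpha 0.05; power 0.80; no change in controls.

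**Assumptions.** The document prints no means, SDs or effect sizes, so 134 cannot be rebuilt. I therefore solve for the T2 effect *d* (in SDs, equal on both outcomes) that gives the stated 80%. Time is taken as a factor, and half of *d* is present at T1.

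**Method.** Noncentral F (Hotelling type). For a pattern v = (T1 effect, T2 effect) in units of *d*, let q = v′V⁻¹v. For two equally affected outcomes with correlation 0.30:

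λ = (n/2) · d² · q · 2/(1 + 0.30)

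**Covariances of (T1, T2), unit SD**
- Change from T0: variances 2(1 − 0.6) = 0.8 and 2(1 − 0.4) = 1.2; covariance 1 − 0.6 − 0.4 + 0.6 = 0.6.
- Adjusted for T0: variances 1 − 0.6² = 0.64 and 1 − 0.4² = 0.84; covariance 0.6 − 0.6 × 0.4 = 0.36.

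**q for the pattern (0.5, 1)**
- Interaction, T0 free: 2(0.25) − 2(0.5) + 1.333 = 0.833
- Interaction, T0 adjusted: 2.059(0.25) − 2(0.882)(0.5) + 1.569 = 1.201
- T2 minus T0: 1/1.2 = 0.833
- T2 adjusted for T0: 1/0.84 = 1.190

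**Calibration.** Setting the 4-df interaction (4 and 129 df) to 80% power gives d = 0.537. Check: λ = 33.5 × 0.537² × 0.833 × 1.538 = 12.4. The T2-minus-T0 contrast has the same q and hence the same λ, but spends 2 df instead of 4.

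**Joint two-outcome power at 67 per arm, d = 0.537**

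| Effect at T1, T2 | Planned interaction (4 df) | Interaction, T0 adjusted (4 df) | T2 − T0 (2 df) | T2 adjusted for T0 (2 df) |
|---|---|---|---|---|
| d/2, d | 0.80 | 0.93 | 0.89 | 0.97 |
| d, d | 0.96 | 0.99 | 0.89 | 0.97 |
| d, d/2 | 0.96 | 0.98 | 0.32 | 0.44 |
| d, 0 | >0.99 | >0.99 | 0.05 | 0.05 |
| d/2, 0 | 0.55 | 0.57 | 0.05 | 0.05 |

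In the first row, 80% power would need about 54 per arm for T2 − T0 and 39 for T2 adjusted for T0.

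**Sensitivity.** Effect ratios of 0.5 to 1.5 between the outcomes and an outcome correlation of +0.30 or −0.30 change the back-solved *d* (first outcome 0.31 to 0.65 SD). They leave the first-row powers for the planned test and the two T2 contrasts unchanged, as well as the planned test's powers in the last two rows. With a share *a* of the effect at T1, q for the planned test is 2a² − 2a + 1.333. This is smallest at a = 0.5, so half at T1 is the case least favourable to the planned test. Change proportional to time would give a between 5/13 = 0.38 and 5/11 = 0.45; at 0.38, q is 0.862, only about 3.5% higher.

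**The case against.** The strongest reply is that test and sample size agree: {14} powers an interaction hypothesis and {20a} tests an interaction. A reader might infer that the primary analysis departs from its sample size basis, or that the trial is underpowered. The documents support neither. The stated 80% belongs to the planned type of test, and the lower figure is inefficiency against an alternative, not a shortfall.

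A reader might also infer that a passing T1 effect will be declared a success. No such rule is written. The objective does not require persistence, and a true T1 difference would be a real effect. The probabilities above 0.99 and of 0.55 in the last two rows are power to detect such a difference, not error rates. They show only that a significant interaction says nothing specific about T2.

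Two further points stand. The degrees of freedom assume categorical time, which {20a} does not state; a linear-time interaction would lose nothing against T2 − T0 under a linear pattern. And the omnibus test protects against an early effect that fades, which is plausible when the game lasts four weeks and T1 falls at week 5.

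That contrasts are often left to an analysis plan does not dispose of the point. This document itself states the test and places the effect at T2, and the two do not answer the same question.

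**Conclusion.** The point holds as a gap in specification and efficiency. No primary visit or contrast is named, the clinically important change is defined at T2, and the interaction alone cannot show that change.

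Under gradual change, adjusting for T0 lifts joint power from 0.80 to 0.93 with the test otherwise unchanged. Directing it to T2 as well gives 0.97. The T0 adjustment helps or does no harm in every pattern examined. The gain from choosing T2 is conditional: it is small once T0 is adjusted for, and it reverses if the effect peaks at T1 and fades (0.44 against 0.96). The case for T2 is therefore mainly that it matches the effect the sample size defines.

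These sizes rest on a back-solved effect, categorical time and an assumed share at T1. The change should be made before analysis.

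**What to change.** State in {20a}: 'The primary test is the joint two-outcome intervention–control difference at T2 from the same mixed model, with T0 as covariate or T0 means constrained equal between arms. Each outcome's T2 difference is then reported under a stated multiplicity rule. The T1 difference is secondary and the overall interaction is supportive.' Say there that time is a factor, and align the hypothesis wording in {14}.

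The cost is wording plus one contrast in MIXED, using data already collected. Controls receive the game only after follow-up, so T2 remains a randomised comparison. The downside is that an effect present at T1 but fading by T2 has less power and counts only as secondary. If the sponsor regards T1 as the key visit, it should name T1 before analysis and realign {14}. The T0 adjustment should be kept either way.

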#### Sibling adjustment to the disability of the brother or sister

The Sibling Perception Questionnaire (SPQ; originally by Carpenter & Sahler [40] and adapted by Lobato & Kao [41]) measures the impact of the disability on the sibling and the sibling’s attitude towards the disability. The questionnaire has a total of 22 items on four subscales: Interpersonal, Intrapersonal, Fear, and Communication. The Dutch version [42] of both the parent-report version and the child-report version will be used in the current study. In this study, the word “illness” in the items will be replaced by “disability.” The items can be answered on a 4-point Likert scale (1 = never to 4 = often). An example of an item is: “I feel sad about the disability of my brother/sister.” In the main data analysis, the 18-item composite Negative Adjustment Scale, which is composed of the sum of the Interpersonal, Intrapersonal and Fear subscales, will be used, because a previous study [41] found that the separate subscales have low internal consistency. The internal consistency of the Negative Adjustment Scale was found to be acceptable to good with Cronbach’s alphas of 0.79 (child-report) and 0.74 (parent-report).

In addition, parents will be asked to provide a written answer to three open-ended questions about the adjustment of the sibling to the disability of the brother or sister. The siblings will be asked to verbally answer these three open-ended questions. Their answers will be audiotaped. When there is no consent for audio recording, the researcher will type down the answers of the sibling.

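### The joint test on the two primary outcomes has no direction and is followed by no per-outcome contrast, so a significant result does not show that quality of life or adjustment improved

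*Protocol article*

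**What the plan says.** The Objectives section asks whether the game is "more effective in improving sibling quality of life and adjustment to the disability of the brother or sister" than the waiting list. Two outcomes are named and joined by *and*.

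The section on statistical methods for primary and secondary outcomes says that "the main effects of intervention and time, together with the interaction effect between intervention and time, will be included in the model". It then says: "The primary objectives will be analyzed multivariate, whereas the secondary objectives are analyzed univariate". On multiplicity it adds only "For the latter, the Bonferroni correction will be used to determine the alpha level", which refers to the secondary objectives. Child and parent reports are modelled apart, and Cohen's d is to be calculated.

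The Sample size section uses the same framework. It derives "the required sample size to conduct multivariate linear mixed models for the primary outcomes quality of life and sibling adjustment", and "The sample size is estimated with an alpha of 0.05 and a target power of 0.80 and is based on an interaction effect hypothesis". It adds: "The correlation between the outcomes is estimated to be 0.30".

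On scoring, the adjustment outcome is an aggregate named for negative adjustment: "the 18-item composite Negative Adjustment Scale, which is composed of the sum of the Interpersonal, Intrapersonal and Fear subscales, will be used". For the PedsQL, the Quality of life section prints item anchors running from never to almost always, with a problem-worded example item. It does not say which way the summary score runs.

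**The concern.** A multivariate interaction test asks whether the arms differ in change over time on at least one outcome, in any direction. The objective asks something narrower: did quality of life improve, and did adjustment improve? Three things are needed to get from one to the other, and the text supplies none of them:

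- model terms that separate the two outcomes;
- a contrast for each outcome;
- a requirement that the contrast be favourable.

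The protocol's Discussion ties open release of the game, and its use by care organisations, to its being shown effective. What counts as showing that on two primary outcomes should be settled before the data are seen. As written, a significant joint result could come from a gain on one scale alone, or from a gain on one and a loss on the other.

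**Working it through.** **The plan's own figure.** The required 134 (67 per arm) cannot be rebuilt, because the means, standard deviations and expected changes are cited and not printed. It is taken as given. The question is how the joint test behaves at that size.

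**Inputs from the Sample size section.** n = 67 per arm; alpha 0.05; correlations over time 0.60 (T0–T1), 0.60 (T1–T2) and 0.40 (T0–T2); correlation between outcomes 0.30 in size; variance factor 1.2.

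**Assumptions.** Effects in SD units, both outcomes coded so that positive means benefit: quality of life a = +0.5; adjustment b = 0 or −0.2. The sign of the between-outcome correlation ρ under that coding is not stated, so both signs are run.

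**Simple model: joint F test of the T0–T2 change, 2 and 131 df, no variance factor.**

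- Variance of change: v = 2(1 − 0.40) = 1.2
- Noncentrality: λ = (n/2) × (a² − 2ρab + b²) / [v(1 − ρ²)]
- Here n/2 = 33.5 and v(1 − ρ²) = 1.2 × 0.91 = 1.092
- b = 0: λ = 33.5 × 0.25 / 1.092 = 7.67
- b = −0.2, ρ = +0.30: λ = 33.5 × (0.25 + 0.06 + 0.04) / 1.092 = 10.74
- b = −0.2, ρ = −0.30: λ = 33.5 × (0.25 − 0.06 + 0.04) / 1.092 = 7.06

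**Fuller model: T0–T1 and T0–T2 changes on both outcomes, 4 and 129 df, variance factor 1.2, half the effect assumed present at T1.**

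- The change covariance matrix per outcome, before the factor, has variances 2(1 − 0.60) = 0.8 and 1.2, and covariance 0.6 − 0.4 − 0.6 + 1 = 0.6.
- For the pattern (0.5, 1) the quadratic form is (0.25 × 1.2 − 2 × 0.5 × 0.6 + 0.8) / (0.8 × 1.2 − 0.6²) = 0.5 / 0.6 = 1/1.2, the same as for the T2 change alone.
- So λ is the simple-model value divided by 1.2, now spread over 4 df.

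| Quality of life | Adjustment | ρ | λ simple / fuller | Rejection, simple | Rejection, fuller |
|---|---|---|---|---|---|
| +0.5 SD | unchanged | ±0.30 | 7.67 / 6.39 | 69% | 48% |
| +0.5 SD | 0.2 SD worse | +0.30 | 10.74 / 8.95 | 83% | 64% |
| +0.5 SD | 0.2 SD worse | −0.30 | 7.06 / 5.88 | 65% | 45% |

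**Reading the table.** Under either sign the joint test rejects often while one primary outcome has not improved. Whether harm on the second outcome raises or slightly lowers the rejection rate depends on ρ. At +0.30 a gain paired with a loss is more surprising to the test than a gain alone, so the rate rises. At −0.30 it falls a little.

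**The case against.** The strongest reply is that an omnibus test followed by outcome-specific interpretation is a recognised approach. The protocol nowhere says that success will be declared from the joint test alone. It plans Cohen's d and commits to publishing positive and negative results, so a worsening would be visible. Detailed model syntax is ordinarily left to a fuller document, and the sentence listing the terms also serves the secondary and exploratory analyses.

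Much of this stands. It rules out four stronger readings that a reader might infer:

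- **That the two scales run in opposite directions.** The protocol does not say so. The printed PedsQL anchors, like the negative adjustment score, point towards more problems. The name of the PedsQL summary score hints at a reversal, but none is described. The joint test is in any case unaffected by recoding either scale.
- **That benefits would cancel.** This needs the two outcomes to be pooled under one interaction term. The word multivariate, and the between-outcome correlation in the sample size calculation, argue against that.
- **That the trial is underpowered through a wrong sign on the 0.30.** The protocol does not show what was entered.
- **That effectiveness will be declared on the joint test alone.** The protocol gives no success rule of any kind.

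What the reply does not remove is the gap itself. The article does fix the terms, the joint analysis and the alpha, and it words the aim as improvement in two named outcomes. An effect size shows direction but is not a decision rule.

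**Conclusion.** The point holds at moderate severity. The stated primary analysis is a non-directional joint test, run separately for each informant, with no outcome factor among its listed terms and no directional contrast per outcome. A significant result would not show that either outcome improved, or which one.

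The size is illustrative. It rests on assumed effects of 0.5 and 0.2 SD, 67 per arm, the protocol's time correlations and, in the fuller model, half the effect at T1. Rejection is about 48–69% with adjustment unchanged. With adjustment 0.2 SD worse it is about 64–83% if the benefit-coded correlation is +0.30, and about 45–65% if it is −0.30. The conclusion does not depend on the sign of the correlation; only the ordering of these figures does.

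**What to change.** 1. Specify the bivariate model with outcome and its interactions with intervention and time, including the three-way term.
2. State the scoring direction of both primary scores, and check that the sign of the 0.30 correlation in the sample size calculation matches that coding.
3. Within each informant's analysis, if the joint test is significant at 0.05, test each outcome's own intervention-by-time contrast at 0.05. With two outcomes this is closed testing, so no further alpha is spent within that informant's analysis. The joint test and the follow-up contrasts must cover the same time points for this to hold.
4. Claim improvement only for an outcome whose contrast is significant in the favourable direction. A contrast spanning both T1 and T2 has no single direction, so name the one that decides, for instance the T0–T2 change.

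The cost is a few lines of analysis text and two extra contrasts per informant, with no new data. The downside is that a significant joint result alone no longer supports a claim on both outcomes. The stated 80% power belongs to the joint test and does not carry over to each outcome's own contrast.

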#### Perceived social support

The Social Support Scale for Children (SSSC) [45] is a child-report scale that consists of four 6-item subscales: Parent Support, Classmate Support, Teacher Support, and Close Friend Support. In the current study, the Dutch version [46] of the scale will be used. The items have a “structured alternative format.” The child first has to choose which of two “types” of kids they are alike, for example “Some kids have parents who don’t really understand them” or “Other kids have parents who really do understand them.” Then the child has to choose if that is "sort of true for me" or "really true for me". The items are scored from 1 to 4, with higher scores representing higher levels of perceived support. The internal consistency was good, with Cronbach’s alphas between 0.72 (Classmate Support Scale) and 0.81 (Close Friend Support Scale), and support for the validity of the scale was found [47].

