#### Sibling relationship

Sibling relationship with the brother or sister with a disability is measured using two different measures. One that is completed by the sibling and one that is completed by the parent.

The Pictorial Assessment of Interpersonal Relationships (PAIR) [48] is an instrument that assesses the characteristics of a close relationship through drawings. In the current study, we use part of the instruction as described by Guidotti et al. [49]. Siblings will be asked to draw themselves with their brother or sister while doing something. The siblings receive an A4 paper, a pencil, and a set of crayons. They can take as much time to complete the drawing as they want. After they made the drawing they will be asked which figure represents whom and what they are doing. The drawings will be assessed by two independent investigators on six different scales: Cohesion, Distancing, Similarity, Value, Emotions, and Conflict. For each subscale, scores can be administered following a standard assessment procedure, which is elaborately described in the manual. The way of scoring differs per scale. In a study with siblings of children with autism spectrum disorder, the inter-rater reliability was good, with Cohen’s kappa larger than 0.90 [49]. Significant correlations between the subscales and total score, and support for discriminant validity were found [48].

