The Parental Expectations and Perceptions of Children’s Sibling Relationships Questionnaire (PEPC-SRQ) [50] is a 27-item parent-report questionnaire that assesses the expectations and perceptions that the parent has of the sibling relationship of their children. On the original Perceptions scale, the parents rate the frequency, how problematic it is, how easy it is to improve, and how much they would like help with that, for each behavior. Because of the relevance to the research question, in the current study only the Perception scale will be used, and only the frequency of the behaviors will be rated by the parents. The questionnaire consists of three subscales: Warmth, Agonism, and Rivalry/Competition. At the end of the questionnaire, the parent is also asked to rate the overall quality of the sibling relationship of their children. The frequency of the behaviors is rated on a 5-point Likert scale (1 = never to 5 = always). The overall quality of the sibling relationship is rated on a 7-point Likert scale (1 = very poor, to 7 = extremely good). An example of an item is: “Loyalty or sticking up for one another.” The questionnaire was translated to Dutch by a team of researchers experienced with the population (e.g., LV) using the WHODAS 2.0 Translation package (version 1.0) [51]. The internal consistency of the original subscales is acceptable to good, with Cronbach’s alphas of 0.86 on Warmth, 0.73 on Agonism, and 0.76 on Rivalry/Competition. Support for construct validity was found [50].

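### Single-step Bonferroni for the secondary outcomes is valid but needlessly conservative; Holm's step-down procedure gives the same error control and never rejects less

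*Protocol article*

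**What the plan says.** The section on statistical methods for primary and secondary outcomes {20a} draws this line: "The primary objectives will be analyzed multivariate, whereas the secondary objectives are analyzed univariate". It then adds, for the secondary objectives, "For the latter, the Bonferroni correction will be used to determine the alpha level". The same section says "Child-report and parent-report outcomes will be analyzed separately". The only outputs it names for these analyses are significance against the adjusted alpha and Cohen's d. It mentions no stepwise procedure and no simultaneous confidence intervals.

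The objectives {7} list five secondary constructs, beginning "1) siblings’ self-esteem, (2) siblings’ perceived social support, (3) sibling relationship with the brother or sister with a disability" and ending with coping skills and the parent-child relationship. Several are measured by more than one score. The social support instrument "is a child-report scale that consists of four 6-item subscales". The sibling relationship is measured twice, once by the child's drawing ("The drawings will be assessed by two independent investigators on six different scales") and once by the parent ("The questionnaire consists of three subscales: Warmth, Agonism, and Rivalry/Competition", plus an overall rating).

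The sample size section {14} rests on the two primary outcomes only: "The sample size is estimated with an alpha of 0.05 and a target power of 0.80". It arrives at 67 children per arm before the allowance for dropout.

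**The concern.** Bonferroni compares every p-value with the overall alpha divided by the number of tests, whatever the other tests show. Holm uses that threshold only for the smallest p-value and relaxes it after each rejection. Bonferroni is sometimes defended as the method that needs no assumption about how the outcomes are correlated, but Holm needs none either. For deciding which outcomes are significant, Bonferroni therefore has no compensating advantage.

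What is at stake is power on the secondary outcomes. The trial was not sized for them, so none of that power is guaranteed, and a correction stricter than it needs to be could leave a real improvement undeclared. The primary analysis is untouched.

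**Working it through.** **Plan's own figure.** The article prints no adjusted alpha for the secondary outcomes, so there is none to reproduce.

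**Inputs from the article.** Alpha 0.05, given in the sample size section and taken as two-sided because the side is not stated. 67 per arm from the same section. Five secondary constructs from the objectives.

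**Assumed inputs.** Standardised effect d of 0.3 or 0.5, and correlation 0.3 between the tests. The article gives neither for the secondary outcomes.

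**1. Thresholds.** Order the m p-values from smallest to largest. Bonferroni compares each with 0.05/m. Holm compares the j-th smallest with 0.05/(m − j + 1) and stops at the first failure.

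| m = 5 | 1st | 2nd | 3rd | 4th | 5th |
|---|---|---|---|---|---|
| Bonferroni | 0.0100 | 0.0100 | 0.0100 | 0.0100 | 0.0100 |
| Holm | 0.0100 | 0.0125 | 0.0167 | 0.0250 | 0.0500 |

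No Holm threshold is below Bonferroni's, so every Bonferroni rejection is also a Holm rejection.

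**2. Error control.** Let m0 of the hypotheses be truly null. When Holm first rejects a true null, all m0 of them are still in play, so the threshold in force is at most 0.05/m0. The chance that any of the m0 null p-values falls below 0.05/m0 is at most m0 × 0.05/m0 = 0.05, whatever the dependence. This is the guarantee that Bonferroni gives.

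**3. Single-test power at the Bonferroni level.** For two groups of n, power ≈ Φ(d√(n/2) − z), where z is the two-sided critical value.
- d = 0.5: 0.5 × √33.5 = 2.894; at alpha 0.01, z = 2.576; Φ(0.318) = 0.625.
- d = 0.3: 0.3 × √33.5 = 1.736; Φ(−0.839) = 0.201.

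**4. Bonferroni against Holm by simulation.** Five tests, 67 per arm, correlation 0.3, 200,000 replicates. The entries are average power per true effect.

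| Effects truly present | d | Bonferroni | Holm |
|---|---|---|---|
| 1 of 5 | 0.5 | 0.626 | 0.627 |
| 3 of 5 | 0.5 | 0.626 | 0.664 |
| 5 of 5 | 0.5 | 0.625 | 0.731 |
| 1 of 5 | 0.3 | 0.200 | 0.201 |
| 3 of 5 | 0.3 | 0.201 | 0.215 |
| 5 of 5 | 0.3 | 0.201 | 0.236 |

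With three of five effects real at 0.5 SD, the family-wise error is 0.019 under Bonferroni and 0.035 under Holm. Holm uses error allowance that Bonferroni leaves unspent and stays below 0.05. The chance of at least one true rejection is essentially the same: 0.893 against 0.894 in that setting, and 0.431 under both at 0.3 SD.

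**5. Where Holm would start.** This depends on the family. Five constructs give 0.05/5 = 0.010. Counting each listed score once gives 1 (self-worth) + 4 (social support) + 6 (drawing) + 3 + 1 (parent questionnaire and overall rating) + 2 (coping) + 1 (closeness) = 18, so 0.05/18 = 0.0028. Six instruments give 0.0083. Separate families by informant, counted by instrument, give 0.05/4 = 0.0125 for the child and 0.05/2 = 0.025 for the parent. Holm's advantage in step 1 holds under every one of these.

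**The case against.** The strongest reply is that Bonferroni is valid, so the plan states nothing wrong. That stands, and it is why this point is an improvement only.

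A second reply is that the gain is small where it matters. The article's own background describes small effects for earlier sibling interventions and for serious games, so 0.5 SD on every secondary outcome is optimistic. This also stands: at 0.3 SD with five tests the gain is about 1 to 4 percentage points, and nil if a single effect is real. The calculation is moreover a simple two-group comparison, whereas the plan tests a group-by-time interaction in a mixed model over three occasions. The figures show the direction and rough size of the gain, not this trial's actual power.

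A third reply is that Holm gives no simple simultaneous confidence intervals. That is true in general, but the article promises only an alpha level and Cohen's d, so no planned output would be lost.

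A reader might go further and infer that the plan is defective because the divisor is not printed and the threshold could be anything from 0.010 to 0.0028. The document does not support that. It is a condensed journal article, and the list of tested scores and the resulting divisor are commonly left to the full protocol or analysis plan, which are not shown. Nor are those two thresholds limits, as the other readings show. A reader might also infer that each construct should be cut to one score. That would demote one of the two sibling-relationship measures, which the article includes on purpose to cover both child and parent.

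**Conclusion.** The point holds as a minor improvement to a valid choice. Holm controls the family-wise error of the secondary outcomes at the same 0.05 with no added assumption, and for each hypothesis its power is never lower and usually higher. It would be too much to say that it has strictly more power in every sense, because the chance of finding at least one effect is practically unchanged.

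Under the assumptions used (67 per arm, five tests, correlation 0.3, two-group approximation), the per-test gain is about 4 points with three of five effects real and 11 points with all five real at 0.5 SD. At 0.3 SD it is about 1.4 and 3.5 points. The gain is close to zero if only one effect is real. The primary conclusions do not depend on it.

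**What to change.** Replace the Bonferroni sentence in the statistical methods section {20a} with: *Holm's step-down procedure at overall alpha 0.05 will be applied to the secondary outcomes.* Apply it over the family of secondary tests that the full protocol or analysis plan defines, and keep both the child drawing and the parent questionnaire for the sibling relationship.

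The cost is one sentence, with no new data and no change to the models or the sample size. It should be made before anyone has seen results by arm; the article's blinding of the analysts leaves room for that. The one thing given up is simple simultaneous confidence intervals, which the article does not plan to report.
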